### Randomization and allocation concealment

A randomization sequence will be generated by an independent statistician who does not participate in this study, using R software (Version 3.5.0; R Foundation for Statistical Computing, Vienna, Austria). Randomization will be stratified based on four Korean medicine hospitals, and then block randomization will be used to approximately equalize the number of participants in each group. A random code will be delivered in the sealed envelopes, in which the allocated group is written. A delegated investigator in each site will open the envelope in sequence and allocate a participant to either intervention or control arm, only when all the screening criteria are satisfied. Allocation will be concealed until the investigator opens each sealed envelope. The randomization sequence will be kept by the independent statistician or physician during the clinical trial period and concealed until the occurrence of the event predefined as a reason for code-breaking.

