#### Secondary outcomes

#### The secondary outcomes are:

Pain: change in the VAS score between baseline (visit 1) and week 2 (visit 4), week 4 (visit 8), week 6 (visit 12), and 4 weeks after completion of the intervention (visit 13). Additional clinical relevance will be compared as follows;
Based on previous studies [31, 32], the proportion of the minimal clinically important difference (MCID) in CLBP is defined as a 2 cm decrease on the VAS. The proportion of MCID (more than 2 cm decrease on the VAS) between baseline and visit 4, 8, 12, and 13 will be recorded.The proportion of participants who experience more than 30% decrease on the VAS between baseline and visit 4, 8, 12, and 13.The proportion of participants who experience more than 50% decrease on the VAS between the baseline and visit 4, 8, 12, and 13.Disability: to evaluate the physical disability due to low back pain, the Roland and Morris Disability Questionnaire (RMDQ) will be applied [33]. The RMDQ score is calculated by 24 items (in the range 0 (no disability) to 24 (maximum disability)). Change in score in the Korean version of the RMDQ will be compared between baseline and visit 4, 8, 12, and 13.Quality of life: to evaluate quality of life, the EuroQol-5D (EQ-5D) questionnaire will be applied. The EQ-5D measures five dimensions (mobility, self-care, activities of daily life, pain, and anxiety/depression) using a 1–3 scale, and a VAS to rate the current health state using a 0–100 scale [34]; change in the EQ-5D scores between baseline and visit 4, 8, 12, and 13 will be compared.Global assessment: to evaluate participants’ impressions of change, the Patient Global Impression of Change (PGIC) will be applied at visit 12 and 13. The PGIC is measured on 7-point scale (from 1 (completely recovered) to 7 (vastly worsened)) with a score of 1–2 indicating improvement, 3–5 no change, and 6–7 deterioration [35].Economic analysis: to evaluate the intervention-related cost, CEA and cost-utility analysis (CUA) will be conducted. Cost data will be collected separately as follows;

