### Statistical analysis

Continuous variables at baseline will be expressed as means plus/minus standard deviation and statistically tested using the two-sample *t* test or the Wilcoxon rank sum test. Categorical variables at baseline will be expressed as frequencies and statistically tested using the chi-squared test or Fisher’s exact test. If there is a significant difference between groups, the baseline variable will be considered as a covariate for efficacy analysis.

The full analysis set (FAS) will be analyzed primarily, including participants who take at least one dose of Palmijihwang-hwan and complete at least one pain assessment. Also, the per-protocol set (PPS) will be subordinately analyzed, including participants who take more than 80% of the total Palmijihwang-hwan dose and complete the trial. In the FAS analysis, the missing data will be imputed using the method of last observation carried forward. The primary outcome (change in the VAS score between baseline and endpoint) will be tested by analysis of covariance (ANCOVA) or rank ANCOVA (according to normality or homoscedasticity) with factors of group and study site and covariates of baseline values. Continuous variables for the secondary outcomes will also be tested, respectively, by ANCOVA or rank ANCOVA. Categorical variables for the secondary outcomes will be tested by chi-squared test or Fisher’s exact test according to the number of the cells with a value of 5 or less in the contingency table. Every variable predefined in the outcome sections will be compared at each time point, respectively.

The safety set will include participants who receive at least one dose of Palmijihwang-hwan. In safety analysis, the frequency and ratio of adverse events will be applied and compared between the treatment group and the control group using the chi-squared test or Fisher’s exact test. Any abnormal change in blood chemistry tests from visit 1 to 12 will be expressed as frequency and percentage and compared between the treatment group and the control group using McNemar’s chi-squared test, and any change in vital signs between visit 1 and 12 and between visit 1 and 13 will be expressed as change scores and compared between the treatment group and the control group using the two-sample *t* test or the Wilcoxon rank-sum test. Statistical tests will be carried out at 5% significance level (two-sided), using R software (Version 3.5.0 or later; R Foundation for Statistical Computing, Vienna, Austria).

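### The responder and PGIC outcomes are tested without site or baseline VAS, which costs some power but does not inflate type I error; the Fisher rule and the MCID cut-off also need tidying

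*Protocol article*

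**What the plan says.** All references are to the protocol article.

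- **Randomization and allocation concealment:** "Randomization will be stratified based on four Korean medicine hospitals, and then block randomization will be used".
- **Statistical analysis, primary outcome:** the VAS change is tested by ANCOVA or rank ANCOVA "with factors of group and study site and covariates of baseline values".
- **Statistical analysis, categorical secondary outcomes:** "Categorical variables for the secondary outcomes will be tested by chi-squared test or Fisher’s exact test according to the number of the cells". The trigger in full is "the number of the cells with a value of 5 or less in the contingency table". No model or stratified test is named, the number of cells that triggers the switch is not given, and nothing is said about continuity correction.
- **Statistical analysis, covariates:** "If there is a significant difference between groups, the baseline variable will be considered as a covariate for efficacy analysis".
- **Secondary outcomes:** the categorical outcomes are the MCID, 30% and 50% VAS responders at visits 4, 8, 12 and 13, and PGIC (grouped as improved, unchanged or deteriorated) at visits 12 and 13. The MCID is defined as a fall of 2 cm, but the outcome is worded "The proportion of MCID (more than 2 cm decrease on the VAS", followed by the visits.

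**The concern.** The responder outcomes are cut-points of the same VAS that is adjusted for site and baseline when it is analysed as a change score. The 2 cm cut-point is likely to depend on baseline. Eligibility requires more than 4 cm, so 2 cm is nearly 50% of a baseline just above 4 (2/4) but about 22% of a baseline of 9 (2/9). A test that leaves out the stratification factor and the baseline is inconsistent with the design and discards information already collected. At stake is the precision of the clinical-relevance outcomes.

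Two smaller matters sit beside this. The Fisher rule appears to look at observed cells, whereas the chi-squared approximation depends on expected counts. The MCID count leaves out a participant who improves by exactly the stated MCID.

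**Working it through.** **1. The plan's own figure.** The Sample size calculation section gives changes of −26.41 (SD 19.06) and −12.83 (SD 19.45), read here as millimetres.

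- Difference = 26.41 − 12.83 = 13.58.
- Pooled SD = √((19.06² + 19.45²)/2) = 19.26, so d = 13.58/19.26 = 0.705.
- The two-sided t test at 0.05 has power 0.793 with 32 per group and 0.806 with 33, so 33 is right.
- 33/0.8 = 41.25, rounded up to 42 per group, 84 in total. This reproduces. The article gives no planning figure for the categorical outcomes.

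**2. Implied MCID responder rates**, assuming normally distributed change.

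- Treatment: Φ((26.41 − 20)/19.06) = Φ(0.336) = 63.2%.
- Control: Φ((12.83 − 20)/19.45) = Φ(−0.369) = 35.6%.

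**3. Cost of omitting site and baseline.** 4,000 trials were simulated per scenario.

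- From the protocol: 84 participants, four sites, blocked 1:1 allocation, control mean change 1.283 cm, effect 1.358 cm, total SD 1.945 cm (the control SD, used in both arms), response defined as a fall above 2 cm.
- Assumed: site sizes 20, 20, 20 and 24, blocks of 4, baseline 4 + 6 × Beta(1.5, 2.5) cm, and the site SD and baseline slope shown below.
- The logistic column is a likelihood-ratio test with site and baseline VAS in the model. CMH is the site-stratified Cochran-Mantel-Haenszel test.

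| Site SD, baseline slope | Measure | Chi-squared | Fisher | CMH | Logistic |
|---|---|---|---|---|---|
| 0, 0 | power | 0.75 | 0.67 | 0.71 | 0.73 |
| 0.5 cm, 0.4 | power | 0.75 | 0.68 | 0.74 | 0.77 |
| 1.0 cm, 0.6 | power | 0.77 | 0.69 | 0.79 | 0.86 |
| 0, 0 | type I error | 0.060 | 0.037 | 0.058 | 0.061 |
| 0.5 cm, 0.4 | type I error | 0.048 | 0.027 | 0.049 | 0.057 |
| 1.0 cm, 0.6 | type I error | 0.039 | 0.021 | 0.049 | 0.053 |

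The simulation standard error is √(0.05 × 0.95/4000) = 0.003 for type I error and √(0.75 × 0.25/4000) = 0.007 for power. Chi-squared is uncorrected. Its 0.060 in the first scenario cannot come from omitted terms, because none has an effect there; exact enumeration at 35.6% in both arms gives 0.054. As site and baseline effects grow, the unadjusted tests become conservative.

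**4. The Fisher rule.** Exact enumeration of all 2×2 tables at 42 per arm, taking one observed cell of 5 or less as enough to trigger Fisher (an assumption), against any expected count below 5. Rates other than 63.2% and 35.6% are assumed.

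- 63.2% v 35.6%: the rules choose different tests in 0.08% of tables, and power is 0.76 under both.
- 20% in both arms: Fisher is chosen in 24% of tables against 2%, with type I error 0.036 against 0.052.
- 35% v 10%: Fisher is chosen in 76% against 0.3%, with power 0.77 against 0.82. If chi-squared is continuity-corrected, the order reverses: 0.74 against 0.72.

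**5. One table, 5/42 v 13/42.** The smallest expected count is 18 × 42/84 = 9.

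- Uncorrected: χ² = 4² × (2/9 + 2/33) = 4.53, p = 0.033.
- Continuity-corrected: χ² = 3.5² × (2/9 + 2/33) = 3.46, p = 0.063.
- Fisher: p = 0.061.

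**The case against.** The strongest reply is that chi-squared and Fisher are valid comparisons of randomised proportions, and that adjustment here is a preference about efficiency. Much of that stands. A reader might infer that ignoring the strata produces false positives, or that chance baseline imbalance invalidates the result. The documents and the calculation do not support this: the nominal error rate already allows for chance imbalance, and the unadjusted tests become conservative as site and baseline effects grow. The plain likelihood-ratio logistic test was slightly above nominal in the simulations (0.053 to 0.061), so the remedy needs a safeguard of its own. The responder proportions also supplement a VAS change that is already adjusted.

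A reader might also infer from 5/42 v 13/42 that the Fisher rule changes significance. That holds only if chi-squared is uncorrected and one small cell is enough to switch. With the correction all the tests agree. Fisher is valid at any count, so choosing it too often is conservative. The word observed is not in the text either: cells with a value of 5 or less most naturally means observed counts, but the wording is loose.

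The conditional covariate rule does not answer the main point. It acts only after a significant baseline difference, and neither named test can use a covariate.

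**Conclusion.** The point holds as a minor one. The binary secondary outcomes are analysed without the stratification factor and the baseline that the primary analysis uses. The cost in power against an adjusted model runs from none (0.75 v 0.73 in favour of chi-squared when site and baseline have no effect) to about 9 points (0.77 v 0.86) under strong effects. Those effects are assumptions, since the article gives no site variance or baseline slope. The sample size and the primary analysis are untouched.

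The Fisher rule is poorly specified but matters only when responder rates are low, as they might be for 50% responders or at early visits. The MCID mismatch is real and affects only decreases of exactly 2 cm; its size cannot be judged from the documents.

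**What to change.** 1. **VAS responders (MCID, 30%, 50%):** logistic regression with group, site and baseline VAS, using a small-sample correction such as a penalised likelihood. Report the marginal risk difference with its 95% CI. If site cells are too sparse, use the site-stratified Cochran-Mantel-Haenszel test with the Mantel-Haenszel risk difference.
2. **PGIC:** it has no baseline value, so use the site-stratified test.
3. **Any unadjusted test that is kept:** switch to Fisher only when an expected count is below 5, and state whether chi-squared is continuity-corrected.
4. **MCID:** count a responder as a decrease of 2 cm or more, in line with the article's own definition.

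The cost is a few sentences in the analysis plan and a little programming. If site and baseline turn out to have no effect, the adjusted analysis gives up slightly: about 2 points for logistic (0.75 − 0.73) and 4 for CMH (0.75 − 0.71). The penalised version was not simulated. The article reports recruitment as ongoing, so on that status the change can be fixed before outcomes are analysed.

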**Discussion:**

The results of our study will provide the clinical evidence about the efficacy, safety, and cost-effectiveness analysis of Palmijihwang-hwan for CLBP. There will be a chance to provide multiple subdivided influence of this treatment with various outcome measures, but lack of placebo is our limitation.

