## Methods and design

### Objectives

The purpose of this study is to investigate the efficacy, safety, and CEA of Palmijihwang-hwan combined with acupuncture for treatment of CLBP by comparing this with the effects of acupuncture treatment alone.

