### Sample size calculation

We performed sample size calculations to determine the appropriate number of participants. The purpose of this study is to verify the synergic effect of the combination treatment (acupuncture + Palmijihwang-hwan) compared to acupuncture treatment alone, using a visual analog scale (VAS) score for change between baseline and completion of the intervention (6 weeks). However, no study has been conducted to investigate the effects of Palmijihwang-hwan combined with acupuncture in the treatment of CLBP. Thus, we reviewed a similar study conducted in patients with CLBP [27] in which the authors evaluated the efficacy of a herbal formula, Ojeok-san, by measuring the VAS score change between baseline and completion of the intervention (4 weeks) and comparing this with the placebo group in randomized clinical trials of CLBP. In that study, the change in VAS score between baseline and completion of the intervention was − 26.41 ± 19.06 in the treatment group and − 12.83 ± 19.45 in the control group. Based on these data, 33 participants would be required per intervention group for a two-arm study and a two-tailed test with 0.80 power (1-β) at the 0.05 α level, as calculated using G* Power (Version 3.1.9.3) [28]. After assuming a 20% drop out rate, we calculated that we would need to recruit 42 participants per group. Thus, a total of 84 participants will be required.

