## Discussion

Despite the development of medicine, the prevalence of CLBP and related disabilities have increased. Conventional treatments such as medications have been reported to have both benefits and harms [37], and several CAM therapies have been used widely and have proven efficacy and safety [38].

In herbal medicine, a CAM therapy, several randomized controlled trials have been conducted and Gagnier et al [39] have reviewed the effects of several herbal medicines on CLBP. However, these studies investigated the use of single herbal medicines such as *Capsicum frutescens* (cayenne) and *Harpagophytum procumbens* (devil’s claw), and there has been no study of the complex herbal medicines that are mainly used in Korean medicine.

Palmijihwang-hwan was used in this study; this is a representative herbal formula for supplementing kidney deficiency in Korean medicine. Palmijihwang-hwan has been suggested to regulate immunity, peroxidation, and the aging process [40], and to have an effect on diverse diseases including diabetes mellitus [41], dementia [42], and chemotherapy-induced peripheral neuropathy [43].

In LBP, we suggested that Palmijihwang-hwan could help patients who have fatigue, cold sensation, lumbago, reduced muscle strength [44], constant pain, or discomfort behavior [45], which might be helpful in CLBP. In addition, kidney deficiency is one of the most commonly diagnosed causes of CLBP [46, 47]. In the absence of a study on the use of herbal medicine in CLBP, this study will be the opportunity to provide information on the usefulness of Palmijihwang-hwan. Pharmacologically, it may provide the clinical information about the toxicity of A. carmichaelii by safety assessment. The toxicity of A. carmichaelii was known that lowest oral dose was 0.2 g/kg and processed aconitum carmichaelii was 60 g/kg [48] while processed *A. carmichaelii* was 60 g/kg [49].

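### Safety is a stated objective, but the only between-arm safety inference the protocol fixes is a set of 5% tests of no difference, which say little about moderate harm at 42 per arm

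*Protocol article*

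**What the plan says.** The Objectives section gives the aim as to "investigate the efficacy, safety, and CEA of Palmijihwang-hwan combined with acupuncture", compared with acupuncture alone. The abstract's Discussion promises "clinical evidence about the efficacy, safety, and cost-effectiveness analysis of Palmijihwang-hwan for CLBP". The main Discussion adds, in hedged terms, that "it may provide the clinical information about the toxicity of A. carmichaelii by safety assessment".

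The Statistical analysis section sets out the safety comparison item by item:

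- **Adverse events:** "the frequency and ratio of adverse events will be applied and compared between the treatment group and the control group using the chi-squared test" (alternatively, Fisher's exact test).
- **Laboratory abnormalities:** frequencies and percentages, compared between groups with McNemar's test.
- **Vital signs:** "any change in vital signs between visit 1 and 12 and between visit 1 and 13 will be expressed as change scores", compared by two-sample t test or Wilcoxon rank-sum test.

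All tests are two-sided at the 5% level. The safety set is defined as participants who received one or more doses of Palmijihwang-hwan.

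The Sample size calculation section works from the VAS change only, with a "two-tailed test with 0.80 power". It arrives at 33 per group, or 42 per group after 20% drop-out. It states no power or precision for any safety outcome.

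**The concern.** A test of no difference does not suit a safety question in a trial sized for a large efficacy effect. If the herb raised adverse events by a moderate amount, a p-value above 0.05 would still be the usual result, just as it would for a harmless product. The test would not separate the two. A reader of the eventual report needs to know how large an excess the data leave open, and only an interval or an upper bound shows that.

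The protocol does not leave the method of safety comparison open. It names a test for each type of safety data and an alpha level. The point is therefore about a choice the article makes, and not about detail it omits.

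**Working it through.** **1. The plan's own figure.** Inputs from the Sample size calculation section: VAS change −26.41 (SD 19.06) v −12.83 (SD 19.45).

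- Difference: 26.41 − 12.83 = 13.58.
- Pooled SD: √((19.06² + 19.45²)/2) = 19.26.
- Standardised effect: 13.58/19.26 = 0.705.
- The two-sample t test at two-sided 5% needs 32.55, so 33 per arm (power 0.806).
- With drop-out: 33/0.80 = 41.25, so 42 per arm and 84 in total.

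The stated figures reproduce. They are set for an effect of about 0.7 SD on pain.

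**2. Power for adverse events.** The article gives no adverse-event rate and no relevant excess, so the rates below are assumptions. Power is the sum, over all 2×2 tables with n per arm, of Bin(x; n, p_T) × Bin(y; n, p_C) for the tables with p ≤ 0.05. Each cell shows Fisher / uncorrected chi-squared.

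| Control v treatment | 42 per arm | 33 per arm |
|---|---|---|
| 5% v 10% | 0.048 / 0.152 | 0.025 / 0.119 |
| 5% v 15% | 0.203 / 0.364 | 0.119 / 0.291 |
| 10% v 20% | 0.175 / 0.259 | 0.115 / 0.210 |
| 10% v 25% | 0.357 / 0.457 | 0.250 / 0.369 |
| 5% v 20% | 0.443 / 0.595 | 0.293 / 0.493 |
| 5% v 30% | 0.846 / 0.904 | 0.701 / 0.819 |
| 10% v 40% | 0.874 / 0.917 | 0.750 / 0.842 |

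At 42 per arm, Fisher's test passes 80% near 5% v 29% (0.819) and 10% v 37% (0.804). By the normal approximation, 80% power would need 141 per arm for 5% v 15% and 199 per arm for 10% v 20%.

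**3. Power for vital signs.** For the two-sample t test, a 0.5 SD shift has power 0.620 at 42 per arm and 0.516 at 33. A 0.3 SD shift has 0.274 at 42. Power reaches 80% at 0.62 SD with 42 per arm.

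**4. What an interval would show.** These counts are illustrative, treatment v control, 42 per arm.

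| Participants with an event | Fisher p | Risk difference, Newcombe 95% CI (points) |
|---|---|---|
| 4 v 2 | 0.68 | −7.7 to +17.8 |
| 8 v 4 | 0.35 | −6.0 to +24.9 |
| 7 v 2 | 0.16 | −1.9 to +26.3 |

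In each row the p-value reports no significant difference, while the interval leaves open an excess of about 18 to 26 points.

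**5. Zero events.** If an event type is not seen in 42 treated participants, the exact upper bound on its risk is 1 − 0.05^(1/42) = 6.9% (one-sided 95%) or 1 − 0.025^(1/42) = 8.4% (two-sided 95%).

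**6. Whether the comparison can be made as written.** The safety set requires a dose of Palmijihwang-hwan. The control group receives acupuncture only, so read literally it has no members in that set. The same paragraph nevertheless compares the two groups. Steps 2 to 4 assume that both arms are included, which is plainly intended. McNemar's test is for paired binary data and does not fit a comparison of two independent groups.

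**The case against.** The strongest reply is that this is a condensed article. It mentions no confidence interval for any outcome, the primary one included, so intervals may well appear in an analysis plan that is not shown. Per-arm counts will be reported, and from them any reader can compute a risk difference. Sizing on the efficacy outcome is usual in a trial of 84 people. All of this is fair. It rules out saying that safety is judged by tests alone, and it makes this an improvement to a stated method rather than a gap. It does not change the fact that the between-arm inference the article specifies is a null-hypothesis test for each safety item.

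A reader might infer two stronger things. The first is that the trial will treat a non-significant result as proof of safety. The article contains no such rule; it promises clinical evidence on safety and says only that it may inform on toxicity. The second is that a relevant harm would most likely be missed. That depends on its size. It holds for adverse-event excesses of about 10 points. At 15 points it depends on the base rate and the test: with 42 per arm, chi-squared power for 5% v 20% is 60%. It fails at 25 to 30 points, where 5% v 30% and 10% v 40% have 85% to 92% power. It also fails for a 0.5 SD vital-sign shift, which is detected 62% of the time at 42 per arm.

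**Conclusion.** The concern stands in a limited form. The tests the article fixes would leave a moderate excess of adverse events largely unexamined: at 42 per arm, power is 18% to 36% for the 10-point excesses considered and 36% to 60% for the 15-point ones. At 33 per arm the figures are 12% to 29% and 25% to 49%. A non-significant result would be weak information about harm of that size.

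These figures rest on assumed event rates, on both arms being in the safety set, and on one comparison of participants with at least one event. They would shift with other rates. The two drafting errors in the same paragraph, a safety set without controls and a paired test for independent groups, do not depend on any assumption and have to be corrected for the comparison to work.

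**What to change.** In the safety paragraph of the Statistical analysis section:

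- Define the safety set to include control participants who received acupuncture as well as treatment participants who received study treatment.
- For participants with at least one adverse event (overall, treatment-related, serious), report the count per arm and the risk difference with a Newcombe 95% confidence interval.
- Where the treatment arm has no events of a given type, give an exact upper confidence bound.
- Handle laboratory abnormalities in the same way, in place of McNemar's test.
- Report vital-sign changes as mean differences with 95% confidence intervals.
- Label any p-values that are kept as descriptive. State that a non-significant difference will not be taken as evidence of safety, and that the safety conclusion will give the largest excess risk compatible with the data.

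This costs changes of wording in the protocol and analysis plan and a few table columns. It needs no new data, visits or participants. The one downside is a more cautious safety conclusion.

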### Safety assessment

Physical examinations will be performed at the screening visit and at visit 1 and 13. Blood chemistry tests including pregnancy tests will be conducted at the screening visit and visit 12. The blood chemistry test will assess the red blood cell (RBC) count, white blood cell (WBC) count, hemoglobin (Hb), hematocrit (Hct), platelet count, erythrocyte sedimentation rate (ESR), aspartate aminotransferase (AST), alanine aminotransferase (ALT), blood urea nitrogen (BUN), creatinine, electrolytes (Na, K, Cl), and C-reactive protein (CRP). Vital signs, adverse events, and change in medication/treatment will be checked at every visit.

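### Laboratory safety values are summarised only as counts of abnormal change, which gives little chance of seeing a small-to-moderate shift between arms

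*Protocol article*

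**What the plan says.** The Statistical analysis section of the protocol article gives one laboratory safety analysis: "Any abnormal change in blood chemistry tests from visit 1 to 12 will be expressed as frequency and percentage". The resulting counts are to be "compared between the treatment group and the control group using McNemar’s chi-squared test". For vital signs, the same sentence says that any change "will be expressed as change scores and compared between the treatment group and the control group", with either a parametric or a rank-based test for two independent samples.

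The Safety assessment section lists the panel: RBC, WBC, haemoglobin, haematocrit, platelets, ESR, AST, ALT, BUN, creatinine, Na, K, Cl and CRP, 14 markers in all. On timing it says "Blood chemistry tests including pregnancy tests will be conducted at the screening visit and visit 12". It also says "Vital signs, adverse events, and change in medication/treatment will be checked at every visit".

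Safety is one of the stated objectives. The Discussion adds that, pharmacologically, "it may provide the clinical information about the toxicity of A. carmichaelii by safety assessment". The article does not define abnormal change, and it states no laboratory event rate and no power for safety.

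**The concern.** All 14 markers are continuous and are measured once before and once after treatment. If a participant is recorded only as having an abnormal change or not, and abnormal means crossing a reference limit, then movement inside the range does not count. Movement across the limit counts the same whatever its size. Because vital signs are analysed as change scores in the same sentence, the loss for the blood tests is a stated choice and is avoidable.

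At stake is how a null laboratory result is read. The trial hopes to inform on the toxicity of one ingredient, and the blood panel is its only laboratory comparison between arms. If the herbal arm showed a consistent moderate rise in a liver or kidney marker, a table of abnormal counts would probably show no significant difference, and the article plans no estimate with an interval that would reveal the rise.

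**Working it through.** **Inputs from the article.** 33 participants per arm needed, 42 per arm recruited, 1:1 allocation, two-sided 5% tests. Changes of −26.41 ± 19.06 and −12.83 ± 19.45 underlie the sample size.

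**The plan's own figure.** Difference = 26.41 − 12.83 = 13.58. Pooled SD = √((19.06² + 19.45²)/2) = 19.26. Standardised difference = 13.58/19.26 = 0.705. Noncentral t power is 0.793 at 32 and 0.806 at 33 per arm, so 33 is right. 33/0.8 = 41.25, rounded up to 42, so 84 in total. These figures reproduce, but they concern VAS; nothing comparable is given for laboratory values.

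**Assumptions (none is in the article).** Marker normal with SD 1 before and after treatment, correlation r = 0.6, and one upper limit c exceeded by 2.5%, 5% or 10% of untreated values. The herbal arm shifts by δ SD and the control arm does not. Abnormal change means at or below c before and above c after. The counts are compared by two-sided Fisher's exact test at 0.05. Both arms are analysed, with 42 per arm, or 33 after dropout.

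**Counts.** The chance of a new abnormality is P(X ≤ c, Y + δ > c), with X and Y bivariate normal. With the 2.5% limit and δ = 0.5 it is 0.0188 in control and 0.0604 in treatment. With 42 per arm the expected numbers are 42 × 0.0188 = 0.8 and 42 × 0.0604 = 2.5. If no control becomes abnormal, 5 treated cases give p = 0.055 and 6 give p = 0.026. The test therefore needs 6 where 2 or 3 are expected.

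**Measured value.** ANCOVA reduces the residual SD to √(1 − r²) = 0.8. The noncentrality is (δ/0.8)·√(n/2), on 2n − 3 degrees of freedom:
- n = 42, δ = 0.5: 0.625 × √21 = 2.86, power 81%.
- n = 33, δ = 0.5: 0.625 × √16.5 = 2.54, power about 70%.

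Adding site costs three more degrees of freedom and changes these figures by less than one percentage point.

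**Power** (counts: range over limits of 2.5% to 10%):

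| Shift | n per arm | Counts, Fisher | ANCOVA |
|---|---|---|---|
| 0.5 SD | 42 | 2–17% | 81% |
| 0.5 SD | 33 | 1–10% | 70% |
| 0.7 SD | 42 | 9–41% | 98% |
| 1.0 SD | 42 | 41–81% | over 99% |
| 1.0 SD | 33 | 25–66% | over 99% |

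**Sensitivity.**
- With r from 0.4 to 0.8 and δ = 0.5, the same formula gives ANCOVA power from 59% (33 per arm, r = 0.4) to 97% (42 per arm, r = 0.8).
- The kind of analysis already planned for vital signs, a t test on change, uses SD √(2(1 − 0.6)) = 0.894. At 0.5 SD it gives 72% (42 per arm) and 61% (33 per arm). Most of the gain thus comes from keeping the measured value; ANCOVA adds the rest.
- A second model applies shift and cut-off directly to the change, in SDs of change. Over 33 to 42 per arm and abnormal rates of 2.5% to 10% in controls, counts against t test are 0.1–6% against 17–20% at 0.25 SD, 1–23% against 52–62% at 0.5 SD, and 29–85% against 98–99.5% at 1.0 SD.

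**The case against.** The best reply is that this is a preference. Frequencies of abnormal laboratory results are a conventional safety summary, no document promises to detect a mean shift inside the reference range, and vital signs may be handled differently without contradiction. Per-marker means with intervals are also the kind of output that a full protocol or SAP, not shown here, could add. All of that stands. It limits the point to an improvement of what the article states: it does not make the counts wrong, and it does not show that continuous summaries are absent elsewhere.

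A reader might infer that the plan has almost no chance of seeing any real shift. The documents do not support that. They give no marker distribution, limit, correlation or rate. Under the assumptions above, counts detect a 1.0 SD shift in 25% to 81% of trials, while a shift as small as 0.25 SD is largely missed by change scores too. A reader might also infer that false reassurance is certain. No such conclusion is written in the article, and adverse events and vital signs are recorded at every visit.

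It is fair to add that the power comparison assumes things the article does not secure. McNemar's test is for paired data and does not compare independent arms. Blood tests are scheduled at screening, not at visit 1. And "The safety set will include participants who receive at least one dose of Palmijihwang-hwan" would, read literally, leave no control arm. These are separate defects. Correcting all three would still leave the dichotomised analysis with the power shown.

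**Conclusion.** The point holds in a limited form. The only laboratory analysis the article states reduces continuous values to counts, while vital signs keep their scale, and this gives little chance of seeing a small-to-moderate shift between arms. For 0.5 SD, power is about 2% to 17% with 42 per arm and 1% to 10% with 33, against about 80% and 70% for ANCOVA. The direction holds for every limit, correlation and sample size tried; the exact figures depend on the assumed normal marker, on r = 0.6, on 2.5% to 10% of untreated values above the limit, and on reading abnormal change as crossing that limit. It does not extend to large shifts, which counts can find, and it is not a charge that abnormality tables are improper. It is a cheap improvement worth making.

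**What to change.** Keep the table of abnormal values by arm, and state what counts as abnormal. Add for each of the 14 markers the visit 12 value, on the log scale where skewed (AST, ALT and CRP are likely candidates), compared between arms by ANCOVA with the screening value and site as covariates. Report a mean difference, or a ratio for logged markers, with its 95% CI. Use the screening draw as baseline, because the Safety assessment section schedules blood tests only at screening and visit 12. State that these are exploratory estimates and not tests of a safety claim.

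The cost is a few lines of analysis text and a little programming. The blood tests are already planned, and ANCOVA with site and baseline is already the efficacy method. The downside is about 14 additional comparisons, among which an isolated interval excluding no difference can arise by chance (14 × 0.05 = 0.7 expected if no marker truly differs), so they should be read together.
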